#### Efficacy assessments

Clinical examination
At the baseline visit and all follow-up study visits, clinical examination and photographs of the wound bed will be performed to assess the defect size, percent granulation, epithelialization, or wound closure.VAS Pain Scale
At the baseline visit and all follow-up study visits, both in-person and by phone, participants will complete the VAS pain scaleQuality of Life Survey
At the baseline visit and the final study visit (8 weeks), participants will complete the quality of life (QoL) survey.Daily Photographs
Starting at Day 7 until the final study visit (8 weeks), participants will take photographs of the wound bed during the daily dressing changes at home.Aesthetics Survey
At the 8-week final study visit, the investigator will complete the aesthetics survey.Scar Scale
At the 8-week final study visit, the investigator will complete the scar scale.Wound Epithelialization
Starting at Day 7 until the wound has closed, the NetHealth Tissue Analytics software will be used to assess the percent wound epithelialization by tracing the epithelial tissue within the wound and tracing the total size of the wound.Wound Closure
Starting at Day 7 until the wound has closed, the NetHealth Tissue Analytics software will be used to assess the percent wound closure by tracing the wound in each photograph over time.

### Participant discontinuation/withdrawal from the study

Participants are free to withdraw from participation in the study at any time upon request. An investigator may discontinue or withdraw a participant from the study for the following reasons:

Failure to healInfection or abscess which requires discontinuation of the study intervention by removal of the wound matrix followed by routine careUnacceptable adverse eventsIn the judgement of the investigator, further treatment would not be in best interest of patientSubstantial non-compliance by the patient with the requirements of the studyThe patient uses illicit drugs that may have reasonable chance of interfering with resultsPatient is lost to follow-upDevelopment of intercurrent illness or situation which would affect assessments of clinical status and study endpoints to a significant degreePregnancy
In the event a study participant becomes pregnant while on study, the pregnancy will be followed to delivery and maternal and fetal outcomes will be documented.IncarcerationDisease progression which requires discontinuation of the study interventionParticipant meets an exclusion criterion (either newly developed or not previously recognized) that precludes further study participation

### Risks

The inclusion and exclusion criteria for this study were designed to minimize the risks to participants. The plethora of human safety data that is published supports the expectation that the only risk involved with the use of rhPDGF is the potential to increase acute inflammation at the site of application following intervention. The wound matrix is a biocompatible xenograft that is indicated for the management of wounds. It is contraindicated in individuals that have a known allergy to porcine tissue or active infection at the surgical site. The wound matrix should be used with caution in patients with impaired wound healing due to metabolic disorders, autoimmune diseases, or drug treatment. Potential adverse events that may be observed are those that may occur with any surgery including swelling, bleeding, hematoma, pain, and local inflammation or allergic reaction. The only other risks are associated with routine care procedures. Throughout the life cycle of the study, safety assessments will be used to ensure proper monitoring of adverse events. Safety assessments will consist of clinical examinations, evaluation of patients’ medical history, pregnancy testing, and weekly participant surveys. The potential benefits of this investigational drug and device to improve the healing rates and quality of life far outweigh the minimal risks in individuals with complex defects following skin cancer excision.

### Statistical analysis

Categorical and binary data will be summarized using counts and percentages. Continuous data will be summarized using medians and interquartile ranges. All statistical tests will use an α = 0.05 Type I error rate, using two-tailed p-values as appropriate for the specified hypotheses, but 95% confidence intervals will be given primary focus above p-values. Statistical models will be adjusted for relevant baseline covariates which are predictive of the models’ respective outcomes to improve statistical power. Model assumptions will be checked using visualizations and tests as appropriate, with data transformations and alternative models considered when assumptions are dubious.

#### Statistical hypotheses

Primary Efficacy Endpoint:
The null hypothesis is that patients in the rhPDGF-enhanced wound matrix arm will have the same time to 81–100% granulation distribution for skin cancer excision surgical defects as patients in the wound matrix saturated with normal saline arm.The alternative hypothesis is that patients in the rhPDGF-enhanced wound matrix arm will have a different time to 81–100% granulation distribution for skin cancer surgical defects compared to patients in the wound matrix saturated with normal saline arm.Secondary Efficacy Endpoints:
The null hypotheses are that rhPDGF-enhanced wound matrix will demonstrate the same average granulation rate, ordinal scale outcomes, time to epithelialization, epithelialization rate, time to complete healing, wound closure rate, pain scale change over time, or patients’ QoL at 8 weeks adjusted for baseline, as the wound matrix saturated with normal saline.The alternative hypotheses are that rhPDGF-enhanced wound matrix will demonstrate a different average granulation rate, ordinal scale outcomes, time to epithelialization, epithelialization rate, time to complete healing, wound closure rate, pain scale change over time, or patients’ QoL at 8 weeks adjusted for baseline, as the wound matrix saturated with normal saline.

##### Sample size

This study will aim to randomize 40 participants in a 1:1 ratio (20 per arm). To achieve balance in treatment allocation, randomization blocks of 4 (2 interventions : 2 controls) will be stratified by anatomical location, scalp/forehead versus face/neck, and greatest dimension, ≤ 3cm versus > 3cm, of the surgical defect. Time to readiness for a skin graft was used for power calculations; this outcome was replaced in a revision of the study protocol with time to 81–100% granulation of the wound, a more appropriate measure of healing that still aligns with our power calculation assumptions. Based on the prior work in the literature, we assume that patients in the placebo arm will have a median time to 81–100% granulation of the wound of 28 days. Assuming that both arms follow an exponential distribution for this primary outcome and that the intervention arm will have a median time to 81–100% granulation of 14 days, a sample size of 20 participants per arm achieves greater than 50% power to reject a log-rank test (22) corresponding to hypotheses outlined above. We assumed that there would be 5% dropout before end of study in each arm, with uniform dropout over time. Power calculations were performed in R version 4.3.1 (23). Primary analyses will adjust for baseline covariates, which may further improve statistical power. Power across a range of assumptions was calculated and displayed in Table 1.

##### Primary outcome analysis

The primary endpoint is time to 81–100% granulation of the wound based on expert assessment of patient wound photos. The time will be in days based on when both expert reviewers agree on the granulation reaching 81–100% granulation by independent review. This time-to-event outcome will be modeled using a Cox proportional hazards model, conditioning on the treatment arm and relevant baseline covariates, as outlined in the SAP. Patients who drop out before achieving 81–100% granulation of the wound will be treated as censored, which will be assumed non-informative. The effect will be presented as an adjusted hazards ratio with a 95% confidence interval, as well as the marginal hazard ratio after performing standardization. A p-value less than 0.05 will be considered statistically significant, but interpretation will be primarily focused on the 95% confidence interval. Kaplan-Meier plots will be used to visualize the results and assess the proportional hazards assumption. Missing data are expected to be limited but will be handled using multiple imputation if there are insufficient photos to determine a precise day where the primary outcome is achieved. Sensitivity analysis will include individuals who are lost to follow-up before achieving 81–100% granulation of the wound, considering multiple imputations for their 81–100% granulation time based on their trajectory of healing before dropout. The primary analysis will be intention-to-treat (ITT) based on randomized arm, as the investigational product is not available to patients who are not randomized to treatment. Supplementary Bayesian analyses will be used to quantify probability of patient benefit.

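### The primary Cox analysis censors every early exit as non-informative, although the protocol allows withdrawal for reasons that are themselves failures of the endpoint

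*Protocol article*

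**What the plan says.** All references are to the protocol article.

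- **Primary outcome analysis, model:** "This time-to-event outcome will be modeled using a Cox proportional hazards model, conditioning on the treatment arm and relevant baseline covariates".
- **Primary outcome analysis, early exits:** "Patients who drop out before achieving 81–100% granulation of the wound will be treated as censored, which will be assumed non-informative". No reason for leaving is excepted.
- **Primary outcome analysis, sensitivity analysis:** "Sensitivity analysis will include individuals who are lost to follow-up before achieving 81–100% granulation of the wound". Their event times would be multiply imputed from how the wound was healing up to that point.
- **Primary outcome analysis, population:** "The primary analysis will be intention-to-treat (ITT) based on randomized arm".
- **Participant discontinuation/withdrawal from the study:** "An investigator may discontinue or withdraw a participant from the study for the following reasons". The list that follows includes a wound that does not heal, infection or abscess leading to removal of the matrix and then routine care, unacceptable adverse events, and disease progression. Loss to follow-up is a separate item in that list.
- **Secondary outcomes analysis:** time to epithelialization and time to complete healing are analysed in the same way as the primary endpoint.

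**The concern.** Non-informative censoring means that, given arm and covariates, a participant who leaves on a given day has the same future chance of granulating as those still followed. A wound withdrawn because it is not healing contradicts that by definition. A wound whose matrix was removed for infection probably does too.

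Censoring such participants takes treatment failures out of the risk set at the moment of failure. The hazard ratio then describes roughly what would have been seen had no such withdrawal occurred, whereas the article presents it as the intention-to-treat effect of the randomised arm. Interpretation is to rest mainly on the 95% confidence interval, so a shifted estimate matters even where significance does not change. With 20 participants per arm, a few withdrawals are enough to move it.

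**Working it through.** **Step 1. Reproduce the plan's power figure.** Inputs from Sample size and Trial design: 20 per arm, exponential times, medians 14 and 28 days, 5% dropout uniform over time, follow-up to day 56. The test is two-sided at 0.05 (Statistical analysis).

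With λ = ln 2 / median, the probability of an observed event is

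0.95 × (1 − e^(−56λ)) + 0.05 × [1 − (1 − e^(−56λ)) / (56λ)]

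- rhPDGF: 0.95 × 0.9375 + 0.05 × (1 − 0.9375/2.773) = 0.924
- Control: 0.95 × 0.75 + 0.05 × (1 − 0.75/1.386) = 0.735
- Expected events: 20 × (0.924 + 0.735) = 33.2
- Schoenfeld power: Φ(√33.2 × ln 2 / 2 − 1.96) = 51.5%, against 52% in Table 1

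The power table therefore reproduces. It treats dropout as uniform over time, which does not represent withdrawal because of failure.

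**Step 2. Compare the two ways of handling failures.** A fraction of each arm is assumed never to reach the event by day 56 and to be withdrawn. The other wounds follow the planned exponential times. The same simulated participants are analysed twice by Cox regression: (a) censored at withdrawal, as planned, and (b) kept at risk without event to day 56. The failure fractions, the withdrawal times and the premise that these wounds never granulate by day 56 are all assumptions.

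Hazard ratios above 1 favour rhPDGF. Medians are 14 v 28 days, and event times are recorded in whole days from day 7.

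| Failing, rhPDGF / control | Withdrawn days 7–28: censored v kept | Withdrawn days 28–56: censored v kept |
|---|---|---|
| 5% / 5% | 1.94 v 1.82 | 1.86 v 1.81 |
| 15% / 5% | 1.76 v 1.39 | 1.49 v 1.39 |
| 20% / 5% | 1.68 v 1.23 | 1.34 v 1.23 |
| 5% / 15% | 2.07 v 2.15 | 2.15 v 2.15 |

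In participants, 5% of 20 is one and 15% of 20 is three. In continuous time without the day-7 start, the 5%/5% pair for days 7–28 is 1.99 v 1.87. Both values are 0.05 higher and the gap is the same 0.12.

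**Step 3. No difference in granulation times (28 v 28 days; continuous time, withdrawal days 7–28).**

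- 5%/5%: 1.00 v 1.00
- 15%/5%: 0.94 v 0.83
- 5%/15%: 1.07 v 1.21

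**Step 4. Rejection rates at 20 per arm (log-rank, withdrawal days 7–28), censored v kept.**

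- Medians 14 v 28: 5%/5%, 48% v 42%; 15%/5%, 36% v 17%; 5%/15%, 54% v 59%
- Medians 28 v 28: 5%/5%, 5.3% v 5.2%

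**The case against.** **Timing.** Trial design gives 4–6 weeks as the usual time to this degree of granulation, and the assumed control median is 28 days. About half of controls would still be short of the endpoint on day 28, so few wounds would be called failures before then. This stands for failure to heal. Late withdrawal shrinks the 15%/5% gap from 0.37 (1.76 − 1.39) to 0.10 (1.49 − 1.39). Infection can come early, so both windows are shown.

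**Rates.** The plan expects 5% dropout in total, about one participant per arm, and at that level the shift is modest. This also stands. However, the 5% is a planning assumption for dropout in general and does not limit withdrawals for failure or infection.

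**The sensitivity analysis.** Imputing "based on their trajectory of healing before dropout" uses the photographs of a stalled wound, which is a weaker assumption than non-informative censoring. It would therefore be wrong to call that analysis irrelevant. It helps less when infection interrupts a good course and the matrix is removed. It is also worded for loss to follow-up, and it does not alter the primary estimate.

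**Ambiguity.** Dropping out is not defined, the withdrawal section speaks of discontinuing or withdrawing, and the infection item speaks of stopping the intervention. Some of these participants might stay under observation. The article does not say that they do, and it gives no other rule for those who leave. The intention-to-treat sentence fixes the arm, not the handling of exits. The article's pointer to the SAP in this section concerns the model and its covariates; the censoring rule itself is stated here.

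**Conclusion.** The point holds. The non-informative assumption is stated for all early exits, and it cannot be true for withdrawal because of failure to heal or infection with matrix removal.

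The direction of the bias, measured against an analysis that counts these withdrawals as not granulated, depends on the data:

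- No effect and equal failure rates: nil.
- A real benefit, with failures equally frequent or more frequent on rhPDGF: the benefit is overstated.
- Failures more frequent in control: neutral to conservative.

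With medians of 14 and 28 days, the shift runs from 0.05 to 0.12 at 5%/5% and from 0.10 to 0.37 at 15%/5%. At 5%/15% it is nil or slightly against rhPDGF. These figures rest on assumed failure rates and withdrawal times.

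A reader might infer that the rule always favours rhPDGF, that balanced failures alone move the hazard ratio away from 1, or that the type I error is inflated. The documents and the calculations do not support this: with equal failure and no effect the hazard ratio stays at 1.00 and the error rate near 5%. Nor is the power table at fault, since it reproduces.

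**What to change.** In Primary outcome analysis, and in the SAP to match:

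1. Separate stopping the study intervention from ending observation. Continue photographs to day 56 where the participant agrees, and use the granulation time actually observed.
2. Where observation ends because of failure to heal or infection with matrix removal, keep the participant in the risk set as not granulated to day 56 in the primary analysis. Treating it as a competing event is equivalent if the subdistribution hazard is modelled; a cause-specific hazard would reproduce the present censoring.
3. Censor at the last photograph only for loss to follow-up or reasons unrelated to the wound. Class adverse-event and progression withdrawals by whether they concern the wound. Setting all of them to not granulated would be a worst-case assumption.
4. Record the reason for withdrawal, and report the present all-censored rule as a sensitivity analysis.
5. Apply the same handling to time to epithelialization and time to complete healing.

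The cost is protocol and SAP wording, a withdrawal-reason field in the case report form, and continued photographs from those who agree. No extra participants are needed, and no change to the clinical withdrawal criteria is proposed. The downside is that the estimand now includes failures and the hazard ratio may be less favourable. Trial status puts the end of data collection in August 2026. The change should be made before unblinding, because afterwards it could be challenged as driven by the data.

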##### Secondary outcomes analysis

The secondary efficacy endpoints will be analyzed for all randomized participants. Analyses will not be dependent on the findings of the primary endpoint.

The first secondary endpoint is percent granulation over time as measured from daily photos. This endpoint will be rated by two adjudicators and averaged. This endpoint will be analyzed using a longitudinal cumulative probability ordinal regression model, which has been shown to perform well with continuous outcomes (24) and can handle the truncated nature of the outcome variable. The model will condition on the treatment arm and relevant baseline covariates, including a random intercept at the individual level to account for within-individual correlation. Time trends will be modeled using spline functions. The treatment effect results will be presented as an adjusted odds ratio and a marginal odds ratio after performing standardization. The proportional odds assumption will be made and assessed by comparing fitted and observed probabilities under proportional and partial proportional odds; the assumption will be relaxed if the assessment indicates lack of fit. Missing data are handled naturally by mixed-effects models fit by maximum likelihood under a missing at random assumption. If missingness is substantially more than expected, alternative methods such as multiple imputation will be considered. The next secondary endpoint of weekly ordinal scale outcomes will be modeled using the same framework and approach.

The next secondary endpoints are time to epithelialization and time to complete healing based expert review and tracing of epithelial tissue and total wound size using the Tissue Analytics software. These will both be analyzed using the same approach as the primary outcome.

The next endpoint is percent epithelialization over time and wound closure over time measured from the tracings in the photos using the Tissue Analytics software. This will be analyzed using a cumulative probability ordinal regression model, as described for the similar longitudinal percent granulation variables. Longitudinal pain scale will also be modeled in the same framework. These models will be further adjusted for corresponding baseline outcome values. Missing data will be handled by the mixed-effects models as described for the percent granulation endpoint.

Ordinal participant quality of life responses, aesthetics survey variables, and scar scale based on final photos at 8 weeks will be analyzed in the same framework without the random intercept, as outcomes are only collected at baseline and 8 weeks. Models will be adjusted for corresponding baseline outcome variables. Missing outcomes at 8 weeks will not be imputed for those lost to follow-up.

The stratification variables for randomization will be adjusted for as baseline covariates in all models unless the number of degrees of freedom available in a given model prohibits this. Subgroup analyses in the strata defined by these variables will be conducted for wound healing outcomes.

##### Safety analyses

Monitoring and reporting of safety events will be conducted continuously as described in the Data and Safety Monitoring Plan. This section describes the assessment of safety endpoints at the time of final analysis. The frequencies of study-related adverse events and all other safety endpoints will be reported along with the treatment effect on the odds of these events (i.e., the odds ratio) and associated 95% confidence intervals using logistic regression for binary safety outcomes and the same methods for ordinal safety outcomes as those outlined for ordinal secondary endpoints above. Descriptive summaries of all adverse events will be provided.

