#### Safety objectives

The safety objectives for this study will evaluate rhPDGF treatment of complex head and neck wounds in patients who underwent skin cancer excision. This will be assessed by qualitative and descriptive summary of all adverse events associated with the intervention, such as but not limited to, wound size assessment, red skin rash around wound area, burning at the application site, swelling at the application site, bleeding at the application site, pain at application site, skin fibrosis around application site, and local recurrence rate of skin cancer.

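### With 20 per arm, the safety odds ratios promised by logistic regression will often not be estimable for the rarer events; the plan should name a method that survives a zero count

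*Protocol article*

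**What the plan says.** The Sample size section sets the size: "This study will aim to randomize 40 participants in a 1:1 ratio (20 per arm").

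The Safety analyses section covers the final analysis and fixes both the scope and the method. On scope: "The frequencies of study-related adverse events and all other safety endpoints will be reported along with the treatment effect on the odds of these events". On method, it gives 95% confidence intervals "using logistic regression for binary safety outcomes and the same methods for ordinal safety outcomes". It sets no minimum event count and says nothing about what happens when an arm has no events. It also says: "Descriptive summaries of all adverse events will be provided".

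The Safety objectives section is more modest: "This will be assessed by qualitative and descriptive summary of all adverse events associated with the intervention". Its list mixes local reactions that may be common, "burning at the application site, swelling at the application site, bleeding at the application site, pain at application site, skin fibrosis around application site", with local recurrence of skin cancer, which may be rare.

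Two other provisions bear on the point. The opening of Statistical analysis allows alternative models when assumptions are doubtful. The end of Secondary outcomes analysis puts the two stratification factors into all models unless degrees of freedom are short.

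**The concern.** An odds ratio needs events and non-events in both arms. With 20 per arm and a long list of separate event types, some types may well produce no event in one arm. The maximum-likelihood odds ratio then does not exist as a finite number, and the promised interval either cannot be computed or depends on how the software handles the failure. This includes the case in which events occur only on rhPDGF, where a reader would most want a between-arm estimate with honest uncertainty. If the plan names no fallback, one will be chosen after the safety data have been seen.

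**Working it through.** **Inputs.** n = 20 per arm (Sample size). The method is logistic regression with an odds ratio and 95% interval (Safety analyses). The article gives no adverse event rate, so the true rate p is an assumption and a range is shown. The safety section has no figure of its own to reproduce. Table 1's 52% power for medians of 14 and 28 days does reproduce by Schoenfeld's formula: 33.2 expected events give √(33.2/4) × ln 2 − 1.96 ≈ 0.04, or 51.5% power. That confirms 20 per arm but does not bear on safety.

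**Step 1: how often an arm is empty.** With the same true rate p in both arms, let q = (1 − p)^20 be the chance that a given arm has no events.
- At least one arm empty: 1 − (1 − q)²
- Exactly one arm empty: 2q(1 − q)

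| True rate p | q | At least one arm empty | Exactly one arm empty |
|---|---|---|---|
| 2% | 0.668 | 89% | 44% |
| 5% | 0.358 | 59% | 46% |
| 10% | 0.122 | 23% | 21% |
| 15% | 0.039 | 8% | 7.5% |
| 20% | 0.012 | 2% | 2% |

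Solving 1 − (1 − q)² = 0.5 gives p ≈ 6.0%. The chance falls below 10% once p exceeds about 13.8%. Exactly one empty arm peaks at 50%, when q = 0.5 (p ≈ 3.4%). At lower rates both arms are increasingly often empty.

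With unequal true rates, at least one arm is empty in 71% of trials at 2% against 10%, 37% at 5% against 20%, and 13% at 10% against 20%.

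**Step 2: what maximum likelihood does with an empty arm.** Unpenalised fits of 0/20 against k/20 failed with a singular matrix for k = 1. For k = 2 to 5 they drifted to log odds ratios of about 23 to 30, with standard errors from about 38,000 to 1.7 million. No Wald interval can be used.

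**Step 3: whether a profile-likelihood interval rescues it.** Take 3/20 against 0/20.
- Log-likelihood at the maximum: 3 ln 0.15 + 17 ln 0.85 = −8.454.
- Under no difference (3/40 in both arms): 3 ln 0.075 + 37 ln 0.925 = −10.655.
- Twice the difference is 4.40, above 3.84, so the interval excludes 1. Its lower limit is 1.22 and it has no finite upper limit.
- Fisher's exact two-sided p is 2 × C(20,3)/C(40,3) = 2 × 1140/9880 = 0.23.

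**Step 4: the alternatives on the same table.**
- Newcombe risk difference. The Wilson limits are 0.052 to 0.360 for 3/20 and 0 to 0.161 for 0/20. Lower limit: 0.15 − √[(0.15 − 0.052)² + 0.161²] = −0.04. Upper limit: 0.15 + (0.360 − 0.15) = 0.36. The result is 15% (−4% to 36%).
- Firth-penalised odds ratio: 8.2 (0.72 to 1131).

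Both are finite and both include no difference.

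**Step 5: covariates.** With both stratification factors in the model, 2,000 simulated trials per rate (equal strata of 10) showed some form of separation in about 78%, 42%, 16% and 6% of trials at p = 5%, 10%, 15% and 20%. Part of this is separation on a stratum factor, which need not remove the treatment odds ratio.

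**The case against.** A reader might infer that one arm will be empty for most adverse event types. The documents do not support that. They give no event rates, and several listed events are local reactions of the kind seen after any operation; the Risks section says "Potential adverse events that may be observed are those that may occur with any surgery including swelling, bleeding, hematoma, pain". At a true rate of 20% an empty arm is a 2% event. The figure for at least one empty arm also includes trials in which both are empty, where there is no contrast to estimate; exactly one empty arm never exceeds 50% under equal rates. Both objections stand and limit the point to the rarer events.

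The article says only logistic regression. It does not say ordinary logistic regression or Wald intervals, and Firth and exact conditional methods are themselves forms of logistic regression. The choice of estimator could sit in an analysis plan that is not shown. This is fair, and it lowers the weight of the point. But the section commits to an odds ratio for all safety endpoints without condition, and the usual reading of that method fails for sparse ones. The allowance for alternative models addresses doubtful assumptions, not an estimate that does not exist. Dropping covariates does not repair an empty arm.

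A profile-likelihood interval would still give a lower limit. It would, but for 3/20 against 0/20 that limit excludes 1, while Fisher's test, the Newcombe interval and the Firth interval all include no difference. Fisher's test is conservative, so the contrast with it alone overstates the gap; the agreement of the other two is what counts.

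It is also tempting to say that a safety signal would go unseen. It would not: frequencies and descriptive summaries are reported, monitoring is continuous, and an independent safety board oversees the trial. A 3-to-0 imbalance would be visible in the counts.

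**Conclusion.** The point holds in a limited form. For event types with a true rate below about 6% in both arms, at least one arm will more likely than not have no events, and the promised odds ratio and interval will then not be available by maximum likelihood in any trustworthy form. For types at 20% or more the problem is negligible. The size depends on assumed rates that are equal between arms, since the documents give none, and on the target of 20 per arm being met. What is lost is a valid between-arm estimate and interval for the rarer events, not the safety information itself. The consequence is modest, but the remedy costs little and is best fixed before unblinding.

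**What to change.** In Safety analyses, state that each binary safety endpoint will be reported as counts by arm and a risk difference with a Newcombe or Miettinen–Nurminen 95% confidence interval. If an odds ratio is kept, state that it comes from Firth-penalised or exact conditional logistic regression with at most the two stratification factors. Use the same edit to align the odds-ratio plan with the descriptive wording in Safety objectives.

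The cost is a sentence or two in the protocol and analysis plan, using standard software. Trial status puts the end of data collection in August 2026, so the change can still precede unblinding. There are two drawbacks: the simple risk-difference interval is unadjusted for the stratification factors, and any odds-ratio interval for sparse events will be very wide, as the Firth result of 0.72 to 1131 for 3/20 against 0/20 shows.
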